# Does feedback on daily activity level from a Smart watch during inpatient stroke rehabilitation increase physical activity levels? Study protocol for a randomized controlled trial

**DOI:** 10.1186/s13063-018-2476-z

**Published:** 2018-03-09

**Keywords:** Stroke, Physical activity, Technology, Goal setting, Feedback

## Abstract

**Background:**

Practicing activities improves recovery after stroke, but many people in hospital do little activity. Feedback on activity using an accelerometer is a potential method to increase activity in hospital inpatients. This study’s goal is to investigate the effect of feedback, enabled by a Smart watch, on daily physical activity levels during inpatient stroke rehabilitation and the short-term effects on simple functional activities, primarily mobility.

**Methods/design:**

A randomized controlled trial will be undertaken within the stroke rehabilitation wards of the Second Affiliated hospital of Anhui University of Traditional Chinese Medicine, Hefei, China. The study participants will be stroke survivors who meet inclusion criteria for the study, primarily: able to participate, no more than 4 months after stroke and walking independently before stroke. Participants will all receive standard local rehabilitation and will be randomly assigned either to receive regular feedback about activity levels, relative to a daily goal tailored by the smart watch over five time periods throughout a working day, or to no feedback, but still wearing the Smart watch. The intervention will last up to 3 weeks, ending sooner if discharged. The data to be collected in all participants include measures of daily activity (Smart watch measure); mobility (Rivermead Mobility Index and 10-metre walking time); independence in personal care (Barthel Activities of Daily Living (ADL) Index); overall activities (the World Health Organization (WHO) Disability Assessment Scale, 12-item version); and quality of life (the Euro-Qol 5L5D). Data will be collected by assessors blinded to allocation of the intervention at baseline, 3 weeks or at discharge (whichever is the sooner); and a reduced data set will be collected at 12 weeks by telephone interview. The primary outcome will be change in daily accelerometer activity scores. Secondary outcomes are compliance and adherence to wearing the watch, and changes in mobility, independence in personal care activities, and health-related quality of life.

**Discussion:**

This project is being implemented in a large city hospital with limited resources and limited research experience. There has been a pilot feasibility study using the Smart watch, which highlighted some areas needing change and these are incorporated in this protocol.

**Trial registration:**

ClinicalTrials.gov, NCT02587585. Registered on 30 September 2015. Chinese Clinical Trial Registry, ChiCTR-IOR-15007179. Registered on 8 August 2015.

**Electronic supplementary material:**

The online version of this article (10.1186/s13063-018-2476-z) contains supplementary material, which is available to authorized users.

## Background

After stroke, practicing an activity and being active helps increase the speed and/or extent of recovery [1] but it is well-established that most inpatients in stroke rehabilitation settings have low levels of activity [2–4]. Increasing patients’ self-generated activity is possible through reorganizing care [5, 6] and could potentially play an important role in increasing independence.

Another way to increase activity and therefore to improve recovery of independence is to provide tailored feedback on activity and on progress towards goals. This could increase motivation, self-efficacy, and self-generated activity. Accelerometers can be used to record activity [2], and they can also be used to provide feedback; use of daily data by therapists can increase time spent walking [7]. There are several studies investigating the effect of feedback about physical activity from accelerometers to individuals. Some show no effect [8, 9] but some show beneficial effects [7, 10]. Benefits seem more likely if feedback is supported by other motivational support [11]. Most of these studies were published after the design of this project; there are many other study protocols published but not yet completed.

The primary objective of this study is to determine whether patient feedback about the amount of activity undertaken compared to their activity the previous day, provided at fixed time points during the day, will increase patient activity. We hypothesise that, compared to a control group who do not receive feedback from a Smart watch, those who receive feedback on daily activity will have increased physical activity levels, as measured by the activity scores, with no harms. We also hypothesize that this increased activity during inpatient stroke rehabilitation will result in improved mobility, and possibly cognition, arm function, independence in daily activities, and health-related quality of life. A third objective is to investigate the feasibility of setting up large-scale trials in a research-naïve setting. This protocol follows an initial pilot and feasibility study. ([name], [name], [name], [name], [name], [name], [name], [name], [name], [name], [name], [name], [name]: Augmented Feedback of Daily Activity on Physical Activity Levels after Acute Stroke: a pilot randomised controlled feasibility study, in preparation).

## Methods

This study was originally registered with ClinicalTrials.gov on 30 September 2015 (NCT02587585). The original registration was for both the initial pilot and feasibility phase, now completed (submitted for publication), and this phase, which has been adjusted from the original in the light of the pilot phase. The trial was also registered with the Chinese Clinical Trial Registry (http://www.chictr.org.cn/showprojen.aspx?proj=12091) on 8 August 2015 (ChiCTR-IOR-15007179). As part of this registration it was also considered by the Chinese National Ethics committee and given a favourable opinion; the certificate is within the registration details, and has reference number ChiECRCT-20150034 (see http://www.chictr.org.cn/uploads/file/20151009090354.JPG). All research will be in compliance with the Helsinki Declarations and the Research Governance Framework for Health and Social Care. Informed consent will be obtained from all participants before involvement in the study.

The trial sponsor is The Second Affiliated Hospital of Anhui University of Traditional Chinese Medicine, Hefei, Anhui Province, China. The public contact is [name], the scientific contact is [name]. This protocol (6 February 2017) has been amended from the original registered protocol (30 September 2015) in the light of the feasibility study; data will not be collected at 6 months because this is not practical. This study started after the feasibility phase, on 20 April 2016 and by 6 February 2017 (date of original submission) had recruited 88 of a target of 200 people.

The study team (ZX, HD, YD) confer by video-phone conference every 2–4 weeks. The local committee is the Smart Watch Activity Feedback Trial Committee (SWAFT), whose members are given in the title page. They meet to resolve any local practical problems. There is no additional data monitoring committee because harmful effects are considered improbable and the study will be short. The primary specific funding body did not undertake an external peer review of the protocol.

### Design

This study is an efficacy, single-blind, randomized controlled trial with the assessor blinded to the group allocation. Participants cannot be blinded to group allocation and ward staff will not be. The intervention being studied is for all patients to wear a Smart watch throughout a normal working day (0800–1700 hours) from Monday to Friday for up to 15 days. They will be randomly assigned, using concealed allocation, to one of two groups where the watch gives:Feedback on amount of physical activity (movement) undertaken, two hourly for the first 8 hours and then for the last 1–2 hours (dependent on the battery life) orNo feedback about the physical activity levels during a 3-week intervention period.

All other interventions (medication, physical therapy) will be kept to their normal routine.

The flow of the study is shown in Fig. 1. Patients will be recruited from all admissions to the rehabilitation wards in the Second Affiliated Hospital of Anhui University of Traditional Chinese Medicine, a large urban hospital. Only patients admitted for rehabilitation after a recent stroke will be approached. The procedure used needs to be compatible with normal clinical practice.

**Fig. 1 Fig1:**
[figure not shown]
Consolidated Standards of Reporting Trials (CONSORT)-style flow diagram

Two questions will be used for initial screening:Can the patient follow a two-stage command, judged clinically?Was the patient walking without help from another person before this stroke?

All subjects who answer “yes” to both questions are eligible and will be entered into the consent and selection process. An investigator will explain the consent form, and allow the person ample time to read through the consent form and ask questions. If they agree, they will acknowledge consent by signing the form. All potential participants will have up to 24 hours to decide whether they want to partake in this study. All actual participants will have given informed consent, signed by them or by an independent witness if necessary, before they are registered.

Patients will be eligible if they:Are aged 40–75 yearsHad onset of stroke less than 4 months agoAre being admitted for rehabilitation for the first timeWere able to walk at least 10 m prior to stroke, without help of another person; use of equipment allowedHave sufficient cognition to participate in the study and testing procedures (clinically judged, because there are no valid short cognitive measures to assess ability to consent and participate)Can follow a 2-stage command (e.g. pick up an object, put it on the table)Have sufficient visual function to see the watch feedback (clinically judged)Have the capacity to consent and then give consent to participate in the study

Entry may be delayed after admission if a person satisfied all other criteria but was not yet able to follow a 2-stage command. In this case, 3-day follow up will be performed, and the patient will be eligible if they then meet that criterion. This was added to allow for patients transferred within 1 or 2 weeks of a stroke, and patients who become confused by the move from another hospital. Patients admitted a second time within the study period will be excluded.

Participants will be randomly assigned to one of two groups: (1) feedback of activity levels; or (2) no feedback of activity levels (i.e. control group). A block stratified randomization approach with two strata will be used, based on walking speed at the time of recruitment. A threshold of 0.42 m/s [12] will be used to define two groups: slow walkers (< 0.42 m/s) unlikely to walk in the community, and moderate-fast walkers (> 0.42 m/s). People unable to walk at the time of recruitment will be classified as slow walkers. The block size will be 5.

Once recruited, the recruiting doctor will inform the research office personnel, who are not blinded, and they will then undertake allocation. Allocation will be performed using a computer program in Microsoft Excel to allocate groups and generate numbers for each stratum (slow walkers or not slow walkers); the allocation will be made by the research office staff after registration. The research office will then notify the ward about the patient’s allocation by telephone. The researchers who will be performing all assessments will remain blinded to group assignment throughout the study.

The participants’ rehabilitation programmes will continue as normal, with no change in relation to this study. Therapists will not specifically be informed about a participant’s group, but may learn this. However therapists will not specifically encourage use of the feedback (or the opposite).

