#### Data handling and analysis

The data will be collected by researchers on the ward using prepared forms. The forms will be given to the research office where they will be entered into an Excel spreadsheet database. The paper forms will be stored in secure, locked files. De-identified and encrypted data will then be sent electronically on a weekly basis to Oxford Brookes University where they will be checked (a) for obvious errors (e.g. data outside the possible range) and (b) for missing data. If needed, the research centre in Hefei will be contacted to clarify apparent errors and to confirm whether missing data are truly absent. The electronic data will be stored in a secure database at Oxford Brookes University, but all investigators will have free access to all electronic data.

The following measures will be compared between the two intervention groups: Barthel ADL index, Rivermead Mobility Index, Fatigue Severity Scale, Montreal Cognitive Assessment, WHO Disability Assessment Scale, EuroQol 5D-5L, and length of inpatient stay. Data will be analysed based on the intention-to-treat principle.

Descriptive statistics will be calculated for demographic characteristics and compliance data. The independent samples or the chi-square (X^2^) test will be used to assess differences between group means and frequencies at baseline, the test being chosen according to data type. Measures that differ significantly between the two groups will be included as covariates in statistical models comparing interventions. The distribution of data will be analysed.

SPSS v23 will be used to investigate progression within groups by regression analysis. The frequency that each person achieves their activity goal, as set automatically by the watch, will be explored within the intervention groups at discharge from inpatient rehabilitation.

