For outcome data, the linear mixed models (LMM) procedure in SAS 9.4 will be used to determine the mean changes in measures, as response variables, according to two intervention regimes (intervention and control) and three repeated measurements, using baseline as a covariate. Distribution of the data will be checked according to various methods of analysis, which are employed at different stages of the study. The analysis of outcome, which will be based on LMM, assumes a Gaussian distribution that can be checked and tested by standard methods. However, we also note that LMM is, in general, quite robust to violation of the distributional assumptions.

This model treats all factors as categorical, and so different types of data can be used. Further and based on the differences in least squares (marginal) means between the two groups (intervention vs control), provided by LMM analysis, power, effect size (Cohen’s d) and their 95% non-central confidence limits will be calculated. Analysis will be used for each outcome measure. The “group” term is the intervention group; the “time” term is the assessment time point. The group-by-time interaction effect will reveal if there is a greater change over time in one group compared with the other.

For a sample size estimate, we used a conservative estimate of the standardised effect size of change in physical activity levels from the initial assessment to discharge from inpatient rehabilitation (i.e. the first phase of the study) as our primary outcome of interest. Our pilot work suggests an effect size of 0.12, and for alpha 0.05 and power 0.95 for repeated measures with three measurement points, we expect a sample of 182 to be adequately powered. From pilot work we expect 10% to drop out, and so we propose to recruit 200 patients.

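### Randomisation is stratified by walking speed but the stated outcome model omits the stratum, so the reported standard error of the group contrast may be too large

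*Protocol article*

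**What the plan says.** **Allocation.** The protocol article, Methods, Design, says: "A block stratified randomization approach with two strata will be used, based on walking speed at the time of recruitment". The cut-off is 0.42 m/s, and "People unable to walk at the time of recruitment will be classified as slow walkers". Group numbers are generated separately for each stratum. On blocks it says "The block size will be 5"; the split within a block is not given.

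**Outcome model.** Data handling and analysis describes a linear mixed model for the change in each outcome measure, "according to two intervention regimes (intervention and control) and three repeated measurements, using baseline as a covariate". Two between-arm results are drawn from it:

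- Effect sizes and confidence limits are "based on the differences in least squares (marginal) means between the two groups (intervention vs control), provided by LMM analysis".
- For change over time: "The group-by-time interaction effect will reveal if there is a greater change over time in one group compared with the other".

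**Other covariates.** The same section gives one rule: "Measures that differ significantly between the two groups will be included as covariates in statistical models comparing interventions".

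The article nowhere says that the analysis is stratified by, or adjusted for, the randomisation stratum.

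**The concern.** Stratified allocation removes chance differences between the arms in walking ability, so the estimated group difference varies less from trial to trial. A model without the stratum does not take account of this. The variance between strata stays in the residual, and the reported standard error describes a less efficient design than the one that was run.

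The covariate rule does not repair this. It adds a measure when the arms differ significantly at baseline, and stratified blocks are there to prevent such a difference in walking speed. The variable that the design singled out is thus among those least likely to be picked up.

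At stake are confidence intervals that are wider than they need be and some loss of power. Recruitment ended at 160 against a target of 200 (Trial status), so there is little precision to spare.

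**Working it through.** **1. The plan's own figure.** Inputs from Data handling and analysis: "Our pilot work suggests an effect size of 0.12, and for alpha 0.05 and power 0.95 for repeated measures with three measurement points"; the result is 182, with 10% dropout and 200 to recruit. Assumptions not in the document: the effect size is Cohen's f, the correlation between measurements is 0.5, sphericity holds, allocation is 1:1, and the test is the group-by-time interaction.

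- λ = f²·N·m/(1 − ρ) = 0.0144 × 182 × 3 / 0.5 = 15.72
- Degrees of freedom: (2 − 1)(3 − 1) = 2 and (182 − 2)(3 − 1) = 360
- Power = 0.952. The smallest N is 181, or 182 with equal arms, so the figure reproduces.
- Dropout: 182 / 0.90 = 202.2, so 203 against the stated 200.

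With ρ = 0.3 the N is 252, and with ρ = 0.7 it is 110. A between-group test at ρ = 0.5 needs 604. The 182 therefore appears to rest on the interaction, and the stratum plays no part in it.

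**2. Group contrast: effect of leaving the stratum out.** The document gives no prognostic strength for the stratum, so R² below is an assumed partial R² beyond baseline.

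- Overstatement of the standard error: 1/√(1 − R²) − 1
- Actual two-sided type I error of the unadjusted test: 2Φ(−1.96/√(1 − R²))
- N with the stratum that matches 182 without it: 182(1 − R²)

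| R² | SE overstated by | Type I error | Matching N |
|---|---|---|---|
| 0 | 0% | 0.050 | 182 |
| 0.02 | 1.0% | 0.048 | 178 |
| 0.05 | 2.6% | 0.044 | 173 |
| 0.10 | 5.4% | 0.039 | 164 |
| 0.20 | 11.8% | 0.028 | 146 |

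**3. Simulation check of the group contrast.** N = 182, blocks of 5 within stratum split 2:3 or 3:2 at random, analysis of covariance on baseline, stratum uncorrelated with baseline, and an assumed effect of 0.42 for power.

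| R² | Model | Mean reported SE | Actual SD of estimate | Type I error | Power |
|---|---|---|---|---|---|
| 0.10 | without stratum | 0.149 | 0.143 | 0.039 | 0.81 |
| 0.10 | with stratum | 0.141 | 0.142 | 0.047 | 0.84 |
| 0.20 | without stratum | 0.149 | 0.135 | 0.031 | 0.82 |
| 0.20 | with stratum | 0.133 | 0.132 | 0.046 | 0.88 |

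The estimate is unbiased under both models. At R² = 0 the two models do not differ; both give a simulated type I error of 0.055, which shows the size of the simulation error. With baseline and stratum correlated at 0.5, the results at the same partial R² are similar (at 0.20, type I error 0.034 without and 0.048 with the stratum).

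**4. Group-by-time interaction.** Random-intercept mixed model, three time points, N = 182, 40 simulated trials per scenario; mean standard error of the interaction at the last time point:

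| Scenario | No stratum | Stratum main effect | Stratum-by-time |
|---|---|---|---|
| Strata change at the same rate | 0.1463 | 0.1463 | 0.1464 |
| Strata change at different rates | 0.1506 | 0.1506 | 0.1467 |

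A main effect does nothing for this test. Stratum-by-time reduces the standard error only in the second scenario, by 1 − 0.1467/0.1506 = 2.6%.

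**The case against.** The strongest reply is that this is a condensed article. Naming the stratum in the model is a typical detail of an analysis plan, and that plan is not shown. The covariate rule adds measures and does not say that no others may enter, so nothing in the text conflicts with adjusting for the stratum. This is right as far as it goes: a reader might infer that the protocol rules the stratum out, and it does not. But the article goes beyond silence. It states the model and a route for covariates, and the stratum is in neither. Followed as written, the plan would usually omit it.

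The second reply is that baseline is already a covariate. The primary outcome is activity measured at the unaffected wrist, with each person's first day as baseline, and a two-level split of walking speed may add little to that. This stands, and it is why the range must start at zero. Against it, the baseline is a single day sampled 20% of the time, and a noisy baseline need not absorb everything.

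The third reply is that stratified allocation already delivers most of the gain. This also stands: at R² = 0.10 the actual SD of the estimate is 0.143 without the stratum and 0.142 with it. What is wrong is mainly the reported standard error.

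The fourth reply is that a main effect leaves the interaction test unchanged. This is correct, and the remedy has to allow for it.

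**Conclusion.** The point holds for the least squares means contrast. The stated analysis does not reflect the stratified allocation, so the reported standard error is too large and the test conservative. The overstatement is 0% to about 12% over an assumed partial R² of 0 to 0.20, and about 5% at 0.10. That the text omits the stratum is clear. Confidence in the size of the gain is only moderate, because the document gives nothing from which to estimate R². Severity is minor to moderate.

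Three stronger readings are tempting but not supported:

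- **That the results would be biased or falsely positive.** They would not: the estimate is unbiased and the error is on the conservative side.
- **That a definite number of patients' worth of information is lost.** At R² = 0.10, 160/(1 − 0.10) = 178, or 18 patients, but that R² is an assumption and the loss may be zero.
- **That the sample size of 182 is wrong for this reason.** It reproduces as an interaction calculation that does not involve the stratum, and a stratum main effect would not alter that test.

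**What to change.** Pre-specify the randomisation stratum (slow or unable to walk versus faster, as randomised) as a fixed effect in every between-arm model, the primary one included, whatever the baseline significance tests show. Where the group-by-time interaction is the test, add stratum-by-time as well, and state that this term helps only if the strata change at different rates.

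The cost is 1 degree of freedom for the main effect and one per additional time point for stratum-by-time. No new data are needed, since the stratum is already recorded for allocation.

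### A single fixed block size of 5 for two groups, with no stated ratio, leaves every complete block unequal and could make some assignments deducible

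*Protocol article*

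**What the plan says.** All quotes are from the protocol article, Methods, Design, including the paragraphs on randomization that follow Fig. 1.

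- Arms and concealment: "They will be randomly assigned, using concealed allocation, to one of two groups where the watch gives" either feedback or no feedback. No ratio is given here or elsewhere in the article.
- Strata: "A block stratified randomization approach with two strata will be used, based on walking speed at the time of recruitment". The cut is at 0.42 m/s.
- Blocks: "The block size will be 5". This is one value, and the article does not say how five places are divided between two arms.
- Allocation: "Once recruited, the recruiting doctor will inform the research office personnel, who are not blinded, and they will then undertake allocation". The timing is also given: "the allocation will be made by the research office staff after registration".
- Disclosure: "The research office will then notify the ward about the patient’s allocation by telephone". On blinding: "Participants cannot be blinded to group allocation and ward staff will not be".

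The eligibility list in the same section leaves cognition and vision to clinical judgement, and the screening question on following a two-stage command is also judged clinically. The Discussion says that ward doctors collected the research data. Trial status gives 160 patients at the end of recruitment, against a target of 200.

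**The concern.** Permuted blocks serve to keep the arms in their planned ratio throughout recruitment. For two arms with no declared unequal ratio, a block of five cannot do that: each complete block is at best three to two. The article therefore implies either an undeclared 3:2 ratio or a rule for varying the larger arm that it does not describe.

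The second issue is concealment. Holding the list in an office and allocating after registration hides the next entry. It does not hide past entries, and the ward is told these by telephone. With one fixed block size, past entries in a stratum carry information about the next one. Where entry depends partly on clinical judgement, someone who expects a particular arm has some room to let that influence who is entered. The intervention is given openly and the primary outcome is behaviour, so selection of that kind would bear directly on the main comparison.

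**Working it through.** **1. The plan's own sample size.** Data handling and analysis gives effect size 0.12, alpha 0.05, power 0.95, three measurement points and N = 182. The type of effect size is not named. Reading it as Cohen's f for the group-by-time interaction with two equal groups, the noncentrality is λ = f²·N·m/(1 − ρ). The correlation ρ = 0.5 and sphericity are assumptions, since neither is stated.

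- λ = 0.12² × 182 × 3 / 0.5 = 15.72, with 2 and 360 degrees of freedom; power = 0.952.
- The smallest even N reaching 0.95 is 182, so the figure is reproduced.
- With ρ = 0.3, 0.4, 0.6 and 0.7 the required N is 252, 216, 146 and 110. The match is therefore only weak evidence that 1:1 was intended.

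**2. Balance, if all blocks are complete.**

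- Constant 3:2: 0.6 × 200 = 120 and 80; 0.6 × 160 = 96 and 64.
- 3:2 or 2:3 with equal chance: each block adds +1 or −1 to the difference between arms. At 200 there are 40 blocks, so SD = √40 = 6.3. At 160 there are 32 blocks, so SD = √32 = 5.7. The probability of exact equality is about 0.13 and 0.14.

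**3. Cost in power.** Relative efficiency is 4p(1 − p).

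- Constant 3:2: 4 × 0.6 × 0.4 = 0.96. Then 182 behaves like 182 × 0.96 = 174.7, power falls from 0.952 to 0.944, and 182 / 0.96 = 189.6, so about 190 would be needed.
- If all 160 were evaluable, power would go from 0.922 to 0.912.
- Mixed blocks, with a difference of 6 at 200 (103 and 97): 4 × 103 × 97 / 200² = 0.999, which is no practical loss.

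**4. Assignments that follow with certainty from earlier ones in the block.** The observer is assumed to know the scheme and all past assignments in the stratum.

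- Constant 3:2 (10 equally likely orders of AAABB): the fifth is always certain (1.0); the fourth is certain when the last two are alike, (3 + 1)/10 = 0.4; the third is certain when the last three are alike, 1/10 = 0.1. The sum is 1.5 of 5, or 30%.
- Mixed (20 orders): an assignment is certain only once one arm already holds three. The fifth is certain with probability 0.4 and the fourth with probability 0.1. The sum is 0.5 of 5, or 10%.

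**5. Comparison with other schemes** (size-5 and fixed-4 rows by exact enumeration, the rest by enumeration or simulation):

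| Scheme | Certain | Best guess correct |
|---|---|---|
| Fixed 5, constant 3:2 | 30% | 72% |
| Fixed 5, 3:2 and 2:3 mixed | 10% | 62% |
| Fixed 4 | 33% | 71% |
| Fixed 6 | about 25% | 68% |
| 4 and 6 varied at random | about 5.5% | 69% |
| 4, 6 and 8 varied at random | about 2.3% | 68% |

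In the constant 3:2 case, always naming the larger arm is already right 60% of the time.

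**The case against.** The strongest reply has four parts.

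- **Balance.** The trial as a whole need not be unequal. Mixed blocks are equal in expectation and stray by only about 6 in 200. The article never declares 1:1, so no two passages contradict each other, and block composition could stand in a fuller document. This stands as far as the totals go: a reader might infer a 60:40 trial, and the article does not support that. It does not rescue the block size, because no further document can make five places divide equally between two arms.
- **Power.** The loss is trivial even in the worst case. This stands.
- **Predictability.** It is not peculiar to five. A fixed block of 4 yields more certain assignments than either version of 5, and on best-guess accuracy randomly varied 4 and 6 (69%) does worse than mixed fives (62%). This stands. The gain from varying even sizes lies in balance and in fewer certain assignments, not in every measure of predictability.
- **Concealment.** A reader might infer that the ward did work out later assignments. The article does not say that the ward knew the block size, or that it was withheld. It refers to more than one rehabilitation ward, lists run separately in two strata, and allocation follows registration. A reader might also take the provision for delayed entry as a means of timing entry. It is limited to patients who meet every other criterion but cannot yet follow a two-stage command, with a recheck at 3 days, so it is not a general option to wait. Clinically judged eligibility is the more plausible route.

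**Conclusion.** The point holds in a limited form. With two arms and a block of five, every complete block is unequal, and the article states no ratio or split that would explain it. How unequal the totals are depends on the undisclosed composition, from a chance difference of a few patients up to three fifths against two fifths. Lost power is not a reason for concern, and its size rests on the assumed correlation.

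The more serious consequence is a weakening of the stated concealment, and it is conditional. The 10% to 30% range applies to an observer who follows each stratum's sequence and knows or infers the block size. The article shows the conditions that would allow this (fixed size, unblinded ward staff, allocations passed on by telephone), but not that it happened. It gives no ground for saying that concealment failed or that selection bias occurred. The defect is clear, its likely effect is modest, and it is cheap to address.

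**What to change.** Recruitment closed on 16 June 2017, so the scheme for the 160 patients cannot be changed. For them:

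- state the intended allocation ratio;
- report how the blocks of five were actually composed, and the number randomized by arm within each stratum;
- state whether those recruiting patients knew the block size;
- include the walking-speed stratum as a covariate in the primary analysis. Data handling and analysis names baseline values and baseline measures that differ significantly, which does not by itself secure this; an analysis plan that is not shown may already do so.

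For any further randomization, use 1:1 permuted blocks of even sizes varied at random, for example 4 and 6, within each stratum, generated in advance and not disclosed to the wards. The difference between arms then never exceeds 3 in a stratum, and about 5.5% of assignments are certain to a fully informed observer. Changing 5 to a fixed even number would restore balance but would not deal with predictability.

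The cost is a few sentences, one table from the existing allocation list and one model term. No extra patients or data are needed.
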